**Fig. 2 Fig2:**
[figure not shown]
A graphical presentation of the availability intervention (e.g. replacing a proportion of higher energy options with lower energy ones)The size of the change will depend upon the baseline ratio of healthier to less healthy products. For example, in worksite cafeterias where 75% of available options are classified as less healthy the intervention would likely involve reducing this to 50% of options being less healthy.The terms ‘healthier’ and ‘less healthy’ are used to reflect that these products are either side of a point in a continuum of healthiness, rather than ‘healthy’ and ‘unhealthy’ which might suggest taking products from either extreme (for more details see Table 1). Using only products that are at the extremes of the healthiness continuum would limit the range of items across which the intervention could be applied.

**Table 1 Tab1:** Example definition of ‘healthier’ vs. ‘less healthy’ options for the availability intervention

Categories	Items	Cut-off	Higher energy	Lower energy
Cooked main meal (excluding breakfast)	Complete main meals	500+ Cals ^a^	e.g. beef lasagne, chilli con carne and rice	e.g. salads, vegetable tagine and couscous
	Main with side to add	300+ Cals ^a^	e.g. hamburgers, battered fish	e.g. vegetable quiche, chicken breast filled with ricotta
	Sides	Added fat	Potatoes: Roast, saute, wedges, chips, mash; Garlic bread; Onion rings; Onion bhaji	Potatoes: Boiled, baked. Rice, couscous
Sandwiches or equivalents	Sandwiches, wraps, panini, baguettes, bagels, pasties	350+ Cals ^a^		
Snacks	Savoury snacks	120+ Cals	e.g. full-fat, baked or vegetable crisps	e.g. popped crisps, popcorn, coconut curls
	Sweet snacks	150+ Cals	e.g. standard chocolate bars, biscuits	e.g. selected cereal bars (Nakd), popcorn bars, rice cakes, lower calorie (small) chocolate bars: Milky Way, Freddo, Fudge
Drinks	Cold drinks (100% fruit juice and smoothies excluded, up to 250 ml bottles)	50+ Cals	e.g. full-sugar soda, flavoured water, juice-based drinks, squashes, energy drinks	e.g. water, diet soda, lower calorie drinks (Vit Hit etc)
Soups		Added cream	Cream based	Broth or tomato based
Dessert	Dessert pot/ice cream	200+ Cals	e.g. mousse, trifle, ice cream	e.g. yoghurt
	Cakes	200+ Cals	e.g. muffins, cupcakes, sponge sandwich	e.g. teacake, fruit loaf
	Served desserts	200+ Cals	e.g. crumbles, pies, fruit tarts	e.g. low-calorie jelly, sorbet

^a^ Based on Change 4 Life recommending a 400 – 600 –600 (Breakfast – Lunch – Dinner) calorie split (leaving some calories for drinks/snacks)

Lunch: With the 600 calorie allowance:

- Allow 100 calories for vegetables

- Allow 200 calories for potato sides

So, for meals that are ‘all-in-one’ (or have a standard accompaniment that can be rolled into the calorie count, e.g. chilli and rice), less healthy cut-off is 500 calories. For meals that come with potato side, cut-off is 300 caloriesiii.LabellingResearch questionWhat is the impact on energy purchased of adding labels showing energy (calorie) content on items purchased from worksite cafeterias?This intervention comprises labels that state the name of a food or drink item together with the energy content written as ‘XXX Calories’. The latter is to be written in the same font type and size as the product name and/or price information, legible and prominent to the customer, rounded to the nearest 5 or 10 calories, and clearly denoting the portion size to which it refers (see Fig. 3 for an example). In keeping with EU regulations, kilocalorie (kcal) and kilojoule (kj) content will be displayed beneath the ‘XXX Calories’.

**Fig. 3 Fig3:**
[figure not shown]
An example of a product displaying energy labelling

## Methods

### Study design

A stepped wedge design [16] (see Fig. 4) was selected, due to being simpler to implement and better able to capture intervention effects than parallel cluster randomised or multiple-treatment reversal (ABAB) designs. Stepped wedge trials are a type of RCT which involve sequential, but random rollout of an intervention over multiple time periods. Stepped wedge trials typically have a baseline period in which observations are made while all participating sites are unexposed to the intervention, and one time period in which all participating sites are exposed to the intervention (at the end of the trial) [16]. As such, this design allows examination of changes in purchasing within each worksite cafeteria depending on the time-period (baseline vs. intervention); as well as differences in purchasing between worksite cafeterias at different time-points of the stepped wedge trial. Each intervention will be evaluated singly, in one of three sets of six worksites. The 18 worksite cafeterias (one cafeteria per worksite) will be allocated to one of these three sets depending on their readiness to start, determined by data collection systems in place. The first six sites to be ready will be allocated to the first intervention ready for implementation: labelling. The remaining 12 sites will be randomly allocated to implement either the size or the availability interventions. The unit of analyses is the worksite cafeteria, not the individuals using the worksite cafeteria (see Fig. 4).

**Fig. 4 Fig4:**
[figure not shown]
A graphical presentation of the stepped wedge design used for each intervention in the study

Within each of the three sets of six worksite cafeterias, the time at which the intervention is introduced will be randomly determined to control for time trends while maximising sample size. Worksite cafeterias will be allocated to a phase of the stepped wedge design by means of random permutations using random variates of the uniform distribution [17]. The randomisation will be performed by a statistician, with the assistance of computer software.

### Sample

Eighteen English worksite cafeterias recruited from companies that are members of the Institute for Grocery Distribution (IGD; comprising 1027 members), selected on the basis of:Number of employees (>350)Mix of office-based and other site types (to recruit sites that are likely to represent different ranges of socio-economic status)Ability to provide weekly data on sales of individual items and their energy content

Worksites from any region within England would be eligible. Managers of identified eligible worksites will be contacted, and given details on the design of the pilot trial, as well as all the requirements regarding participation in the pilot trial, including the range of possible timings for implementing the intervention in the stepped wedge design. Please see Fig. 5 for a CONSORT flow diagram delineating the flow of participating sites through the pilot trial.

**Fig. 5 Fig5:**
[figure not shown]
CONSORT flow diagram

### Measures

#### Feasibility assessment measures

*Feasibility of recruiting and retaining eligible worksites:* measured by recording recruitment rates, and the number of worksite cafeterias dropping-out of the pilot trial (i) post-recruitment, (ii) during the baseline or (iii) during the intervention period.
*Feasibility of implementing the assigned intervention:* determined after initial visits to worksite cafeterias by the research team, discussions regarding suitability with worksite managers and catering teams, and by examining the sales data supplied by the sites. Qualitative interviews with worksite managers will provide an additional measure of potential challenges with implementation of the intervention.
*Acceptability of the interventions:* measured by surveying patrons of the worksite cafeterias regarding acceptability of, and other perceptions concerning, the intervention. Qualitative interviews with worksite managers will supplement the survey data, providing insight into the acceptability of study and assessment procedures.
*Compliance with the study protocol:* assessed via compliance visits coinciding with the initial period of intervention implementation for each randomised worksite.

### Intervention impact measures

#### Primary outcome

Total energy (calories) purchased per time frame of analysis controlling for the total sales/transactions.

#### Secondary outcome

Total energy (calories) purchased per time frame of analysis from (a) intervention items, and (b) non-intervention items controlling for the total sales/transactions.

#### Other measures

Various other measures will be collected that will allow us to estimate the primary and secondary outcomes with greater precision. Covariates examined for all three interventions include: worksite demographic characteristics (age, gender, and dominant occupational status); day of week (if the distribution of the data allows for analysis per day); and weather conditions.

The following will also be recorded for each of the three interventions:i)Size: mean energy (calorie) per product pre-intervention; mean reduction (%) in energy (calorie) per product; mean price pre-intervention; mean reduction (%) in price; mean size of tableware pre-intervention; mean reduction (%) in size of tableware.ii)Availability: proportion of food/drink intervention items that are healthier pre-intervention; proportion of food/drink items that are targeted in the intervention; mean energy (calories) per item pre-intervention; reduction (%) in proportion of intervention items that are healthier from pre-intervention; reduction (%) in energy (calories) per item from pre-intervention; Mean price pre-intervention; mean change (%) in price.iii)Labelling: mean energy (calories) per item pre-intervention; mean energy (calories) per item during intervention.

### Planned analyses

#### Feasibility assessment analyses

Feasibility and acceptability outcomes, including recruitment and attrition rates, will be reported using descriptive statistics. Qualitative assessments gathered via semi-structured interviews with worksite cafeteria staff will be coded and summarised in narrative form.

#### Intervention impact analyses

One of the main aims of this pilot trial is to estimate the effect size of each of the three interventions, to inform the sample size calculations necessary for a future, larger trial. This will be achieved by conducting quantitative analyses using linear mixed models, which will be reported in full in the scientific paper reporting the results of the pilot trial. By estimating intervention parameters, while taking into account the within-site data dependence and controlling for other parameters, mixed models will help define the effect size of each intervention.

The potential impact of each intervention will be estimated in separate linear mixed models examining the impact on total energy (calories) purchased per time frame of analysis controlling for the total sales/transactions, adjusted for calendar time and with random effects for worksite.

If heteroscedasticity due to different worksite sizes (number of employees) is observed and/or if model assumptions are not respected, outcome change of scale would be considered, as well as alternative analyses considering, for example, weighting worksites according to their variance [18]. If mixed model assumptions are not met, generalised estimating equations (GEE) will be preferred.

Initial analyses will be conducted to confirm the selected time frame level of weekly (as opposed to daily) sales. A weekly time frame will be selected if the conditional distribution of the daily outcome is incompatible with the model assumptions (after transformation), and if time-dependence is still present after controlling for total sales/transactions.

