### Procedure

For each of the three interventions, all six worksite cafeterias will initially undergo a baseline period (4 weeks) in which their usual sales are recorded. Sites will then be randomised to implement the intervention at one of six, two-weekly intervals.

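### GEE is the named fallback on six sites per model; with the usual sandwich variance and a normal reference, its standard errors would be about 15-34% too small

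*Protocol article*

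**What the plan says.** The Study design section sets the number of clusters: "Each intervention will be evaluated singly, in one of three sets of six worksites". It also fixes the level of analysis: "The unit of analyses is the worksite cafeteria, not the individuals using the worksite cafeteria". Under Intervention impact analyses, "The potential impact of each intervention will be estimated in separate linear mixed models", each "adjusted for calendar time and with random effects for worksite". The 18 sites are therefore not pooled.

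If site sizes produce unequal variances or assumptions fail, the same section first considers a change of outcome scale and weighting of worksites. It then gives the rule at issue: "If mixed model assumptions are not met, generalised estimating equations (GEE) will be preferred". The article does not say which working correlation, variance estimator, small-sample correction or reference distribution would be used. It states no significance level, test or power. The declared purpose is to estimate effect sizes that will inform the sample size of a larger trial.

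**The concern.** When a mixed model's distributional assumptions fail, the attraction of GEE is its robust (sandwich) variance. That variance estimates the between-cluster variability from the clusters themselves and is justified only when there are many of them. Here there are six, with one site crossing at each step and calendar-time terms to be estimated as well. The rule thus answers one doubtful assumption with a method whose own main requirement is known in advance to be unmet, unless a correction is built in.

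What is at stake is the uncertainty reported around each effect. Intervals that are too narrow would make the pilot's effect sizes look firmer than they are when the larger trial is sized on them.

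**Working it through.** The article gives no power, alpha or precision figure, so there is nothing of its own to reproduce. The check is a simulation of one intervention set with no true effect.

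**Inputs from the article**
- Six sites per model (Study design; Intervention impact analyses).
- Baseline: "all six worksite cafeterias will initially undergo a baseline period (4 weeks) in which their usual sales are recorded".
- Steps: "Sites will then be randomised to implement the intervention at one of six, two-weekly intervals". With six sites this is read as one site per step.
- Length: 4 + 6 × 2 = 16 weekly values per site. This is a reading of the layout; 18 weeks was also run.
- Adjustment for calendar time, form not given.

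**Assumed inputs**
- Gaussian outcome; intra-cluster correlation (ICC) 0.05, 0.3 or 0.8. The article gives no value and plans to estimate it.
- Time as a linear trend, a two-week period factor or a week factor.
- Exchangeable or independence working correlation.
- Variants: serially correlated errors, unequal site variances, a site-varying effect, a sales-type covariate.
- 1,500 to 4,000 runs per setting (Monte Carlo error about 0.6 to 1 percentage point).

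**Results, exchangeable correlation, 16 weeks, 4,000 runs.** SE ratio is the mean uncorrected robust SE divided by the true SD of the estimate. The other columns are rejection rates at a nominal 5%. KC is Kauermann-Carroll, MD is Mancl-DeRouen.

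| Time | ICC | SE ratio | Sandwich, z | Sandwich, t(5) | KC, t(4) | MD, t(5) |
|---|---|---|---|---|---|---|
| Linear | 0.05 | 0.73 | 20.5% | 12.0% | 6.9% | 5.4% |
| Linear | 0.3 | 0.81 | 15.4% | 8.4% | 4.5% | 4.1% |
| Linear | 0.8 | 0.85 | 14.7% | 7.5% | 4.1% | 3.6% |
| Two-week | 0.05 | 0.69 | 21.6% | 12.8% | 6.3% | 4.2% |
| Two-week | 0.3 | 0.73 | 20.1% | 11.3% | 5.3% | 3.2% |
| Two-week | 0.8 | 0.76 | 18.1% | 10.0% | 4.5% | 2.9% |

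With a week factor, the sandwich with z gave 21.8%, 19.6% and 16.9% at the three ICCs.

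**Over all settings run**
- SE ratio 0.66 to 0.85, so the SE is too small by 1 − 0.85 = 15% to 1 − 0.66 = 34%.
- Sandwich with z: about 14-25%. Coverage of a nominal 95% interval is 100 − 25 = 75% to 100 − 14 = 86%.
- Bias of the point estimate: under 0.03 SD.

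**Why both corrections are needed.** If the SE were merely shrunk by a constant factor of 0.81, the rejection rate would be 2 × [1 − Φ(1.96 × 0.81)] = 2 × [1 − Φ(1.588)] ≈ 11%. The simulated rate was 15.4%. The remainder arises because an SE estimated from six clusters is itself very variable. A t reference alone therefore falls short (about 7-14% with t(5)), and so does Mancl-DeRouen with z (about 6-11%). Together they bring the rate close to nominal: Kauermann-Carroll with t(4) about 3.5-7%, Mancl-DeRouen with t(5) about 2-5%.

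**Cross-check.** A standard package's default GEE (400 runs) rejected in 22% (linear) and 18.5% (two-week period) of null trials. The mixed model on the same data, with its assumptions true, rejected in 5.8% and 4.8%.

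**The case against.** Four objections carry weight.

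*The faulted variant is not written in the article.* It names GEE and no variance estimator, and an analysis plan that is not shown may specify a correction. This stands as a limit on the claim: the figures describe ordinary GEE, not a procedure the article spells out. It does not remove the point, because the choice of GEE on six clusters is made here as a stated preference, and the default form of that method is the one that fails.

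*GEE is not invalid with six sites.* A reader might infer that it is. The corrected forms in the table show otherwise, so deleting the fallback does not follow.

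*The plan has no 5% test.* A reader might take the 14-25% as the trial's false-positive rate. No alpha or hypothesis test is stated, the Discussion calls the estimates exploratory, and the point estimate is unbiased. The rejection rate serves only as a gauge of how far the intervals fall short.

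*The mixed model can be just as bad when its assumptions fail, which is the only case that triggers GEE.* This also stands in part. With strong serial correlation (AR(1) 0.5; 1,000 runs per cell, ICC 0.5), a random-intercept mixed model with z rejected in 14.9% (linear) and 18.2% (two-week), against 14.7% and 18.0% for uncorrected GEE. With unequal site variances added, the mixed model was at 17.6% and 17.4%, GEE at 13.5% and 16.9%. At AR(1) 0.3 GEE was the more liberal (15-18% against 11-13%), and with no serial correlation clearly so (14-17% against 5-6%). It therefore cannot be said that the fallback always makes matters worse. It can be said that, uncorrected, it does not cure them, while Mancl-DeRouen with t(5) stayed at 2-4% throughout.

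The rule is also a late resort, after rescaling and weighting.

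**Conclusion.** The point holds in a limited form. Six clusters per model is fixed by the design, and the article prefers GEE there with no stated safeguard. Run in its usual form, that fallback would understate uncertainty by the amounts shown above. Those amounts rest on assumed ICCs, an assumed form of calendar time, a Gaussian outcome and a 16-week reading of the layout. The shortfall appeared in every setting run, but its exact size should not be quoted as a property of this trial.

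The consequence is overstated precision of the pilot's effect sizes, not a biased estimate. The documents do not support the stronger readings that GEE cannot be used with six sites, that the trial has an inflated 5% test, or that the fallback is always inferior to the mixed model. The point ranks as should-fix, because it concerns a conditional fallback in a pilot.

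**What to change.** Amend the one sentence in Intervention impact analyses in either of two ways.

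1. Keep GEE, but only with a small-sample corrected sandwich (for example Kauermann-Carroll or Mancl-DeRouen) and a t reference on about 4-5 degrees of freedom. Name the correction and the degrees of freedom in advance.
2. Use a randomisation test instead. Within each set of six, step timing is allocated "by means of random permutations using random variates of the uniform distribution", which gives 6! = 720 possible orders. This also serves the labelling set, whose membership is not randomised but whose step order is. The test needs no distributional assumption and no large number of clusters. Its limits should be stated: the p-value moves in steps of 1/720, and an interval obtained by inverting the test assumes a constant effect across sites, although the Interventions section expects the content to differ between sites.

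The cost is some programming and wider intervals. In the linear-time, ICC 0.3 case the half-width in units of the true SD goes from 0.81 × 1.96 = 1.59 to 0.91 × 2.776 = 2.53 with Kauermann-Carroll and t(4), about 1.6 times as wide. That extra width is uncertainty the uncorrected interval leaves out.

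### The time-frame rule requires two conditions before moving to weekly data, so residual time-dependence alone leaves a daily model whose standard error for the intervention effect may be too small

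*Protocol article*

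**What the plan says.** All the analysis statements are in the protocol article, Planned analyses, Intervention impact analyses.

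- **Starting position:** "Initial analyses will be conducted to confirm the selected time frame level of weekly (as opposed to daily) sales".
- **Rule, first condition:** "A weekly time frame will be selected if the conditional distribution of the daily outcome is incompatible with the model assumptions".
- **Rule, second condition, joined to the first:** "after transformation), and if time-dependence is still present after controlling for total sales/transactions".
- **Model:** a separate linear mixed model for each intervention, controlling for total sales or transactions, "adjusted for calendar time and with random effects for worksite". The section describes such models as estimating the effect "while taking into account the within-site data dependence".
- **Fallback:** "If mixed model assumptions are not met, generalised estimating equations (GEE) will be preferred".

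On the design, Study design states: "Each intervention will be evaluated singly, in one of three sets of six worksites". Procedure states that "all six worksite cafeterias will initially undergo a baseline period (4 weeks) in which their usual sales are recorded", followed by six two-week steps.

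The document states no autocorrelation, significance level or power. The purpose of the models is to estimate effect sizes that inform the sample size of a larger trial.

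**The concern.** The two conditions address different problems. An unsuitable daily distribution is a matter of shape. Remaining time-dependence is a matter of correlation between days at the same site. Either is a reason to leave the daily level, but the rule acts only when both are present. If the daily outcome is well behaved and its residuals are still serially correlated, the literal rule keeps the daily analysis.

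The named model does not obviously absorb that correlation. Calendar time removes movements shared by all sites. A worksite random intercept makes all days of a site equally correlated. Neither captures runs of high or low days specific to one site. In a stepped wedge, each site's exposure is one unbroken block, so such runs feed directly into the uncertainty of the intervention contrast.

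What is at stake is the stated precision. A pilot that reports intervals that are too narrow passes false confidence in its effect sizes to the planning of the larger trial.

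**Working it through.** The plan has no figure of its own to reproduce, so the check asks how far the model-based standard error departs from the true one.

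**Inputs from the document.** There are 6 sites per intervention. Duration is 4 baseline weeks + 6 × 2 weeks = 16 weeks, with one site crossing over at each step.

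**Assumptions.** There are 5 trading days a week, so 80 days per site. There is no true effect. Daily residuals are AR(1) with lag-1 correlation ρ, after adjustment for calendar time and any covariates. ρ is not in the document, so a range is shown. Calendar time is taken either as a linear trend or as week indicators.

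**Formulas.** Let X hold exposure and calendar time, centred within site, and let R be the AR(1) correlation matrix of a site's days.

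- True variance of the exposure coefficient: the exposure element of (X′X)⁻¹(ΣX′RX)(X′X)⁻¹, in units of the residual variance.
- Variance the random-intercept model reports: E(s²) times the exposure element of (X′X)⁻¹.
- VIF = true variance / reported variance.
- Reported SE / true SE = 1/√VIF.
- Rejection rate of a nominal 5% test = 2[1 − Φ(t/√VIF)], where t is the two-sided 5% critical value.

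**Worked case: ρ = 0.5, linear calendar time, daily data.** VIF = 2.753. SE ratio = 1/√2.753 = 0.603. With 472 residual degrees of freedom, t = 1.965, and 1.965/1.659 = 1.184. The rate is 2[1 − Φ(1.184)] = 23.6%. As a rough check, the long-series factor (1+ρ)/(1−ρ) = 3 gives an SE ratio of 0.577 and a rate of 25.8%.

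**Results** (linear trend / week indicators):

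| ρ | Daily VIF | Reported SE ÷ true SE, daily | Rate, daily | Rate, weekly sums |
|---|---|---|---|---|
| 0.1 | 1.205 / 1.214 | 0.91 / 0.91 | 7.3% / 7.5% | 5.0% / 5.0% |
| 0.2 | 1.458 / 1.481 | 0.83 / 0.82 | 10.4% / 10.6% | 5.4% / 5.3% |
| 0.3 | 1.777 / 1.823 | 0.75 / 0.74 | 14.1% / 14.6% | 5.8% / 5.8% |
| 0.5 | 2.753 / 2.892 | 0.60 / 0.59 | 23.6% / 24.8% | 7.4% / 7.4% |
| 0.7 | 4.761 / 5.164 | 0.46 / 0.44 | 36.8% / 38.7% | 10.9% / 11.0% |

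The weekly column uses the same random-intercept model with a t reference. With a normal reference the weekly rates are about 5.3%, 5.7%, 6.2%, 7.9% and 11.5%.

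**Simulation check.** REML random-intercept fits to daily data, 1,500 runs per setting, gave 14.3-15.0% at ρ = 0.3 and 23.3-24.7% at ρ = 0.5.

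**Residual variance.** E(s²) is 97-99% of its true value at ρ = 0.3, 93-97% at 0.5 and 87-93% at 0.7. The error variance is therefore only slightly low. Nearly all of the shortfall is in the standard error of the effect.

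**GEE fallback.** An exchangeable working correlation with an uncorrected sandwich variance and six clusters was simulated 3,000 times per setting for ρ from 0 to 0.7. It rejected in 13-19% of runs with a normal reference and in about 6-10% with t on 5 degrees of freedom, largely regardless of ρ.

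**The case against.** **Weekly is the plan's preferred level.** The section speaks of confirming weekly. The Sample section makes only weekly sales data an eligibility requirement. Other measures treats analysis by day as something the data may or may not permit. The conjunction may simply be loose drafting for a list of two triggers. That is fair, and it means the daily analysis should not be described as the plan's default. It does not remove the point, because the published rule says something else.

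**The fallback may already apply.** Independent residuals are an assumption of a random-intercept model, so detected time-dependence could trigger GEE. This is possible. But the rule lists model incompatibility and time-dependence as separate items, so it is unclear that serial dependence counts. If GEE is triggered, an uncorrected sandwich with six clusters is itself anti-conservative. A small-sample reference improves it, and the analysis plan may provide one.

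**The figures depend on an assumption.** A reader might infer that the plan's test runs at 14-39%. The document does not support that. Those rates need a residual daily correlation of about 0.3 to 0.7, and adjustment for transactions, day of week and weather may leave less. At 0.1 to 0.2 the rate is 7-11%. No 5% test is stated either, so the rate only measures the error in the standard error.

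**The absence of a serial term is not itself a fault.** A reader might also infer that the model wrongly fixes exchangeable correlation. The article does not spell out the residual covariance, and a condensed article may leave that, the degrees of freedom and any permutation test to an analysis plan that is not shown. What stands is narrower: the article states a selection rule, and the rule does not act on time-dependence alone.

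**Conclusion.** The point holds as a fault in a stated decision rule. On its plain wording, residual time-dependence alone leaves the analysis daily. If the model then has only calendar time and a worksite random intercept, the reported standard error is about 91% of the true one at a daily correlation of 0.1, falling to about 75% at 0.3 and 45% at 0.7. Summing to weeks removes most of this, though not all at high correlation. These sizes rest on AR(1) residuals, a 5-day week and 16 weeks.

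The effect estimate is not biased, so it would be wrong to conclude that the pilot's effect sizes are distorted in direction or amount. Their stated precision is what may be too favourable. Because this is an exploratory pilot with weekly as its intended level, the correction is moderate and not a must-fix. It is worth making because the effect estimates and their precision inform the larger trial's sample size.

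**What to change.** In the time-frame rule, replace *and if* with *or if*, so that either an unsuitable daily distribution or remaining time-dependence selects weekly. Alternatively, fix weekly as the time frame and drop the rule. If daily data are kept while time-dependence remains, state that the model will include a within-site serial-correlation term.

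The cost is one sentence, or one model term if daily is kept, and no new data. Little information is lost by going weekly, because exposure changes only at week boundaries. The downside is that reported intervals become wider where daily residuals are positively correlated, which reflects the real uncertainty.
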